### Determination of sample size

A sample size of 168 will be required to identify a moderate effect size of 0.5 between treatment groups, in a regression model with power = 0.8, alpha = 0.05. An additional 32 participants will be included to allow for an attrition rate of 20% during follow up. The total sample size required is therefore 200. This attrition rate is based on our recent experience in an alcohol dependent population with a high prevalence of comorbidity [53].

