### Procedure

After baseline assessment, all participants will complete a pre-treatment session of motivational interviewing followed by a 1 month “washout” period of abstinence. Symptoms of social anxiety (SPS and SIAS), general anxiety and depression (DASS) will then be reassessed. After reading and signing a written information and consent form, participants will be individually randomised by the sealed envelope method to one of two treatment conditions, of either: i) Treatment for alcohol use disorder comprising 9 weekly sessions of individual CBT for alcohol use disorder; OR ii) Treatment for alcohol use disorder and social anxiety disorder comprising 9 weekly sessions of integrated individual CBT for alcohol use disorder and anxiety disorder.

Each therapy session will last 60 to 90 minutes and will be conducted by one therapist (Clinical Psychologist). Both treatment conditions will have the same therapists and equal exposure to face-to-face treatment, approximately 10–15 hours, over a total of approximately three to five months.

Participants will be encouraged to attend treatment sessions weekly where possible, but will be given a maximum time frame of 5 months from initial assessment in which to complete treatment. Post and follow up assessment time points will be calculated from the end of all treatment sessions (1 motivational interviewing session plus 9 treatment sessions).

Participants will be considered non-completers if they miss more than 2 treatment sessions, or if they fail to complete the course of treatment within five months from assessment. Therapists will make at least 3 attempts to reschedule missed appointments, followed by a handwritten note two weeks after the last phone contact to i) acknowledge client’s decision to leave treatment, ii) encourage return to treatment, and iii) provide information about how this can be achieved. Participants who nevertheless choose to discontinue treatment will be contacted for post and follow up assessments calculated as if treatment were completed 3 months from the initial assessment.

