### Analyses

Random effects regression models will be used to compare the efficacy of the treatment conditions on outcome measures from an intention to treat perspective. Random effect regression models (also known as hierarchical linear or mixed models) have been used in clinical trials involving relapse, and are suited to repeated measures, missing observations, and longitudinal data [99]. Random effects regressions can also account for variance associated with the clustering found with group treatment and multiple treatment sites. Cox regression will be used to determine time from baseline to first drink, time to first heavy drink. Last-point carried forward or multiple imputation will be used to determine the scores of participants who drop-out and are not located at follow-up.

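### The required sample size of 168 does not follow from the printed effect size, power and alpha, which need about 128; the article does not show which figure is wrong, and the error is conservative

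*Protocol article*

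**What the plan says.** The section Determination of sample size in the protocol article gives four figures in one sentence: "A sample size of 168 will be required to identify a moderate effect size of 0.5 between treatment groups". The same sentence places the calculation "in a regression model with power = 0.8, alpha = 0.05". It continues: "An additional 32 participants will be included to allow for an attrition rate of 20% during follow up", and concludes: "The total sample size required is therefore 200".

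Under Procedure, participants are "individually randomised by the sealed envelope method to one of two treatment conditions". No allocation ratio is given. The Analyses section plans random effects regression on an intention-to-treat basis and adds: "Random effects regressions can also account for variance associated with the clustering found with group treatment and multiple treatment sites". The sample-size paragraph gives no sidedness, correlation between repeated measures, intraclass correlation, design effect or multiplicity adjustment.

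**The concern.** A standardised difference of 0.5 at 80% power and 5% alpha is a familiar benchmark, and it needs roughly 64 per arm. The stated 168 is 31% above 128 (168/128 = 1.3125), which is too large a gap to be rounding. The attrition allowance is added separately to reach 200, so it does not explain the excess.

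What is at stake is the record of what the trial was designed to detect and at what error rate. This paragraph is where a reader or analyst looks for the design power and alpha. As printed, at least one of its figures is wrong, or an assumption that produced 168 has been left out.

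**Working it through.** **Inputs.** From Determination of sample size: total 168, effect size 0.5, power 0.8, alpha 0.05, 32 extra for 20% attrition, 200 in all. Assumed because not stated: 1:1 allocation, a two-sided test, and an effect size in standard deviation units.

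**1. Attempt to reproduce 168.** The normal approximation is n per arm = 2(z_alpha + z_power)²/d².

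- 2(1.960 + 0.842)²/0.5² = 62.8, so 63 per arm and 126 in total.
- The exact two-sample t-test gives 63.8, so 64 per arm and 128 in total.
- As a regression, d = 0.5 corresponds to f² = 0.0625. A test of one treatment term needs 128, whether the model holds 1, 5 or 11 predictors. Testing two or three terms jointly gives 158 or 179.
- One-sided testing gives 100 to 102. Allocation of 2:1 gives 144.

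None of these gives 168.

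**2. What 168 evaluable would deliver (84 per arm, two-sided 0.05).**

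- Normal approximation: 0.5 × √(84/2) = 3.240, and 3.240 − 1.960 = 1.280, so power is 0.900. By t-test it is 0.896.
- Effect detectable at 80% power: 2.802 × √(2/84) = 0.432. By t-test it is 0.435.

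**3. The attrition step.**

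- Base of 168: 168/0.8 = 210, and even the simple mark-up 168 × 1.2 gives 202. The 32 added is 32/200 = 16% of those randomised.
- Base of 128: 128/0.8 = 160 = 128 + 32. The 32 fits exactly.
- As planned: 200 × 0.8 = 160 completers, 80 per arm. Then 0.5 × √(80/2) = 3.162, and 3.162 − 1.960 = 1.202, so power is 0.885. By t-test it is 0.882.

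**4. Unstated assumptions that would bring the figure to about 168.**

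| Assumption | Total, normal approximation | Total, t-test |
|---|---|---|
| 90% power, two-sided 0.05 | 170 (84.1 per arm) | 172 |
| 80% power, two-sided 0.05/3 | 168 (83.8 per arm) | 172 |
| 3:1 allocation, otherwise as printed | 168 | not computed |
| Design effect 1.31 to 1.33 on 128 or 126 | 168 | 168 |

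For the last row, 1 + (m − 1) × ICC = 1.333 needs an ICC of 0.083 with clusters of 5, 0.037 with 10, or 0.018 with 20. These cluster sizes are assumed, since the article gives none. The article states none of the four assumptions.

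**The case against.** The strongest defence is that the article condenses a fuller calculation. The planned analysis is a random effects regression, and the Analyses section mentions clustering. An inflation of about 1.31 to 1.33 would take 128 or 126 to 168 with the printed power and alpha both correct. This cannot be ruled out, and it is why the cause must be left open. It does not rescue the sentence. The paragraph offers 168 as the consequence of three named inputs and says nothing of an inflation. Treatment in both arms is individual, so clustering by treatment group does not obviously apply.

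A reader might go further and infer that the printed power or alpha must be the wrong figure. The document does not support that. Besides an unreported inflation, 168 may itself be the mistake, and the attrition figure points towards a base of 128.

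A reader might also infer that alpha was divided by three for social anxiety, alcohol and quality of life, because 0.05/3 lands on 168 under the normal approximation. The article mentions no split of alpha. Its section on primary outcomes names two social anxiety scales, drinks per drinking day, a dependence questionnaire and a quality-of-life scale, so a divisor of three is only one possible grouping. By t-test the same route needs 172.

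The defence is also right about impact: the discrepancy runs in the safe direction.

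**Conclusion.** The point holds as an inconsistency within one paragraph. The printed inputs need about 128, not 168, assuming a 1:1, two-sided comparison of two arms or an equivalent one-term regression test. On those inputs 168 evaluable participants give about 90% power, and the 160 expected to remain from 200 give about 88%.

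The document does not identify the wrong figure. It also gives no ground for calling the trial underpowered for an effect of 0.5: even though 20% attrition leaves 160 rather than 168, power stays above the stated 80%. The consequence is an unreliable statement of the design power and possibly of the intended error rate.

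**What to change.** Restate the sample-size paragraph so that its figures agree, in one of two ways.

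1. If the printed effect size, power and alpha are right, correct the required number to about 128 (160 with 20% attrition). Then report that 200 randomised, with about 160 completing, gives about 88% power for a difference of 0.5 at two-sided alpha 0.05.
2. If 168 is right, state the assumption that actually produced it: higher power, a divided alpha, a design effect or an allocation ratio. Also correct the attrition sentence, because 20% loss from 200 leaves 160, not 168.

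The choice should come from the original calculation, not from whichever assumption happens to give 168. Use a divided alpha in the analysis only if that calculation was based on one. The cost is a few rewritten sentences, with no change in enrolment.

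### The 32 extra participants cover 16% attrition, not the stated 20%: 200 enrolled leaves 160, 8 short of the 168 said to be required, though the 80% power target is still met

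*Protocol article*

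**What the plan says.** All the figures stand together in the Protocol article, under Determination of sample size.

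- The requirement before losses: "A sample size of 168 will be required to identify a moderate effect size of 0.5 between treatment groups", with the conditions "in a regression model with power = 0.8, alpha = 0.05".
- The allowance for losses: "An additional 32 participants will be included to allow for an attrition rate of 20% during follow up".
- The conclusion: "The total sample size required is therefore 200".

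The same section says that the 20% comes from the team's own recent experience in an alcohol-dependent population with much comorbidity, so it is the loss that the investigators expect.

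Two other places bear on the consequence. Under Procedure, participants are "individually randomised by the sealed envelope method to one of two treatment conditions"; the allocation ratio is not given. Under Analyses, the plan is for intention-to-treat random effects models, and "Last-point carried forward or multiple imputation will be used to determine the scores of participants who drop-out and are not located at follow-up".

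**The concern.** Attrition during follow-up is a loss from those enrolled. The allowance therefore has to be sized so that the enrolled number, less 20%, comes back to the required number. Adding 32 to 168 does not do this. At the loss rate that the investigators expect, the published total misses the published requirement.

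What is at stake is the accuracy of a design figure that others will rely on. A reader of the section would believe that 200 enrolled secures 168 with follow-up data at 20% loss, and it does not. Whether power also suffers has to be checked separately against the stated effect size, alpha and power.

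**Working it through.** **Inputs** (Protocol article, Determination of sample size): required number 168; extra 32; attrition 20%; total 200; effect size 0.5; power 0.8; alpha 0.05.

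**Assumptions, because the article does not state them:** 1:1 allocation, a two-sided test, a simple two-group comparison, and effect size as a standardised mean difference.

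**1. The plan's own total.** 168 + 32 = 200, so the addition is right. The source of the 32 is less clear:
- as a share of 168: 32 / 168 = 19.0%
- as a share of 200: 32 / 200 = 16.0%
- 20% of 168 is 33.6, and 168 × 1.2 = 201.6

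The total looks like 168 × (1 + 0.20) taken to a round number. That formula applies the loss to the wrong base.

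**2. The correct inflation.** Enrolled = required / (1 − attrition) = 168 / 0.80 = 210. That is 42 extra, against 32 in the plan.

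**3. What 200 delivers.**
- At 20% loss: 200 × 0.80 = 160. Shortfall: 168 − 160 = 8, and 8 / 168 = 4.8%.
- Largest loss that still leaves 168: (200 − 168) / 200 = 16%.

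**4. Power for an effect size of 0.5 at two-sided alpha 0.05.** With n per arm, the normal approximation is power = Φ(0.5 × √(n/2) − 1.960).

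| Total with data | n per arm | 0.5 × √(n/2) | Normal approximation | t-test |
|---|---|---|---|---|
| 160 | 80 | 3.162 | Φ(1.202) = 0.885 | 0.882 |
| 168 | 84 | 3.240 | Φ(1.280) = 0.900 | 0.896 |

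The 8 participants cost about 1.5 percentage points, and both totals exceed the stated 80%.

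**5. What the stated inputs need.** n per arm = 2 × (1.960 + 0.842)² / 0.5² = 62.8, so 63 per arm and 126 in total (64 per arm and 128 in total by the t-test). Allowing for 20% loss, 126 / 0.80 = 157.5, so 158, or 128 / 0.80 = 160 enrolled. An enrolment of 200 exceeds either figure.

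**The case against.** The strongest reply is that nothing is lost against the stated target. The stated inputs need only 126 to 128 participants with data, and 160 is well above that. The shortfall exists only against 168, which itself does not follow from those inputs. This stands, and it limits the consequence. It does not repair the attrition step, because the article calls 168 the required number and presents 200 as securing it.

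A second reply is that participants who are lost are not simply removed. Random effects models use the visits that were observed, and imputation is planned for those not located. This also stands in part: 160 counts people with follow-up data and is not the size of the analysis set. Imputation does not restore the information in outcomes that were never observed, however, and the plan itself chose to add participants for attrition, so the allowance should agree with its own rate.

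The condensed form of a journal article is no answer here. Every input and the result are printed, and they disagree.

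In the other direction, a reader might infer that the trial is underpowered. One route is to look for a basis that reproduces 168 at 80% power, such as alpha divided by three, and to argue that 160 then falls below 80%. The document does not support this. It states alpha 0.05 and no divided alpha. About 90% power at two-sided 0.05 explains 168 nearly as well (170 by the normal approximation), and on that basis 160 still gives about 88%.

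**Conclusion.** The attrition allowance is arithmetically wrong as printed. The 32 extra participants cover 16% attrition; at the stated 20%, 200 enrolled leaves 160, which is 8 short of 168, and keeping 168 would take 210. This part rests on no assumption beyond reading attrition as a share of those enrolled. Reading it as a share of 168 does not give 32 either.

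The consequence is modest. Under the assumptions listed in the working, power for 0.5 is about 88% with 160 and about 90% with 168, so the stated 80% is met either way. The point is a misstated design figure and should not be read as a finding that the trial is too small.

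The basis of 168 is a separate question. It does not reproduce from the stated inputs, and the attrition error holds whatever its origin.

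**What to change.** Keep 200, and replace the claim that it preserves 168 at 20% loss with wording such as:

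> With 200 enrolled, 20% attrition leaves about 160 with follow-up data (168 if attrition is 16%). Assuming 1:1 allocation and a simple two-group comparison, 160 gives about 88% power for a standardised mean difference of 0.5 at two-sided alpha 0.05.

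The power statement should use only the alpha that the protocol states.

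The cost is one corrected passage and no extra participants. The number expected to have follow-up data falls from 168 to 160, while the power quoted at the stated alpha is about 88%, above the 80% target. Enrolling 210 would also restore consistency, at the cost of 10 more participants, but the stated power target does not require it.

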## Discussion

Alcohol use disorders and social phobia are commonly comorbid despite epidemiological and basic science findings that the two disorders interact to produce greater disability and poorer treatment outcomes. Existing clinical trials [4,5] indicate that alcohol focused treatment will give the best result. These trials did not test integrated treatments based on research into the mechanisms that may underlie the comorbidity and probably treated samples with severe alcohol dependence. Thus this trial will examine an integrated intervention based on basic cognitive and behavioural research in a sample with a range of severity of alcohol use disorders. It is hypothesised that this novel integrated package of motivational interviewing and cognitive behavioural therapy will lead to better overall outcomes across drinking, social anxiety and quality of life. In addition those with more severe levels of alcohol dependence are hypothesised to achieve relatively less benefit from the novel intervention than intervention focused on alcohol alone. This paper describes the trial protocol; companion papers describe the research and clinical basis for the contents of the intervention [63] and the intervention itself is documented in detailed therapist and participant manuals.

The proposed study addresses how individuals with comorbid alcohol use disorders and social phobia are best treated. Through the development and testing of the proposed intervention, the study could potentially define appropriate treatment for adults affected by these problems.

## Abbreviations

CASP: Combined alcohol social phobia.
